**11.8.13. Emotion regulation**

Emotion Regulation will be measured using the Attractive Toy in a Transparent Box task, taken from the Laboratory Temperament Assessment Battery (Lab-TAB) (52). This task is designed to allow for the analysis of the child's emotion regulation and response to blocked goals. During the four minute task the child is asked to retrieve a toy from a locked box using a ring of incorrect keys. The child is allowed to keep the toy following the task. Should the child give any verbal or nonverbal cues during the activity that they wish to end the task then the researcher will do so. Recordings of the activity will be coded for emotion regulation using a standardised rating scale, by raters blinded to group allocation

**11.8.14. Executive function**

The Minnesota Executive Function Scale (MEFS) (53) will be used to carry out an assessment of executive function skill level. The MEFS has high content validity, as well as high convergent validity with other EF assessments. The measure is delivered using a tablet and is an adaptive virtual card-sorting task which takes approximately 4-minutes for the child to complete.

**11.8.15. Prosocial behaviour**

A 'dolls play' task where a short play interaction between child and researcher is recorded. This task is designed to provide an index of the child's prosocial behaviours. Recordings will be coded using a standardised rating scale, by raters blinded to group allocation.

**11.8.16. Genetic variance**

Where participants consent to take part in the genetic aspect of the trial we will collect a buccal (mouth) swab from the child. This will be used to obtain cells to conduct an analysis of genes related to child development and behaviour, including key candidate genes such as BDNF, FKBP5, NR3C1, DRD4, SLC6A4 and 5-HTTLPR. This will allow us to determine how child behaviour relates to the methylation of certain genes and whether the effects of VIPP-SD are moderated by children's genotype. This involves a non-invasive procedure undertaken by trained researchers where a swab is gently rubbed on the inside of the child's cheek to extract cells for genetic testing. Data will be collected, transferred, analysed, and stored in accordance with the Human Tissue Act. Following analysis samples will be stored in the Imperial College tissue bank.

**11.8.17. Feedback questionnaire**

A brief feedback questionnaire will be given to parents at the 5-month follow-up visit. This is closely based on those previously used in ViPP studies in the United Kingdom. Questions explore participant satisfaction and experience of the intervention's helpfulness, enjoyableness, relevance, and format.

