## **11.2. Phase 2**

Following screening, participants who score in the top 20% of population norms will be contacted by a member of the research team to see if they would like to participate in the full study.. For those that are selected, they will be contacted by phone and a date will be arranged for a member of the research team to visit them at home to complete the first assessment visit. At this stage it will be ascertained whether there are two parents in the family and whether both would like to take part.

This first assessment visit will take approximately 90 minutes with each family. During this visit the research team will provide additional written and verbal information about the study, and will allow participants to ask any questions about the study. The purpose of the study will be explained, as well as the procedures participants will be asked to complete. Participants will be informed that they can withdraw from any aspect of the home visits, and from the overall study at any time. The randomisation process will also be explained, so participants are aware that they will be randomly allocated to one of the two groups.

521 **11.3. Blinding**

522 Researchers assessing study outcomes will be blinded to randomised allocation. Participants (i.e. parents and their  
523 children) will be informed of their randomised allocation. In the event of a severe adverse event the Chief Investigator  
524 will be notified and may be informed of the randomised allocation.

525 **11.4. Randomisation**

526 Randomisation lists (one per site) will be prepared by a statistician using 1:1 allocation (ViPP intervention vs treatment  
527 as usual) and appropriate block sizes and uploaded on to InForm (the study electronic data capture system) prior to the  
528 start of the study. Eligible subjects will be allocated online to the next available treatment code in the appropriate  
529 randomisation list.

530 Randomisation will be stratified by treatment centre and by willingness and availability of both parents to be involved  
531 (versus one only).

532

533 **11.5. Follow-up visits**

534 Follow-up assessments will be undertaken in the family home by research assistants who are blind to treatment  
535 allocation, at a time convenient for the family.

536 Participants will be contacted by the research team prior to the visit time or the first post-treatment assessment and they  

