## 548 11.8. Measures

### 549 11.8.1. Pre-PACS

550 The primary outcome measure will be an assessment of the severity of the child's behavioural problems using a  
551 structured investigator-led interview of a parent or caregiver (the Preschool-PACS), at five and twenty four  
552 months after randomisation (the child will be aged 3-5 years at this later assessment point). Where two  
553 parents/caregivers are participating in the trial the Pre-PACS will be completed by the parent who identifies as  
554 being the primary caregiver. The Pre-PACS is a semi-structured assessment of child behaviour problems,  
555 administered by trained interviewers, which yields a score for behavioural problems based on investigator  
556 judgement. To determine pre-PACS scores, caregivers are asked to recall and describe detailed examples of  
557 their child's behaviour over the last week in a range of settings (e.g., in the home, with peers, and in public  
558 settings such as the supermarket). The parent is also asked about how representative the behaviour is of the past  
559 4 months (to ensure the example is typical and characteristic of the child). The interviewer then rates the  
560 severity and frequency of the symptoms on the basis of their professional/clinical judgement and written  
561 definitions and thresholds of the behaviours, validated according to clinical practice. Symptoms are rated for  
562 frequency and severity on two subscales, one measuring ADHD/Hyperkinesis, and the other measuring conduct  
563 problems and antisocial behaviours.

564 The Pre-PACS has high inter-rater reliability and good construct validity, and has been used in previous clinical  
565 trials (e.g., 11-14). Interviewers will be blind to allocation. Semi-structured interviews are the gold-standard  
566 measure for most psychiatric disorders. They are more objective as they use investigator-based criteria for  
567 scoring symptoms, and are thus less prone to parental biases, which are seen when using parent-reported  
568 questionnaires. All PPACS interviews will be recorded for reliability purposes. Recordings will be assessed  
569 periodically to avoid drift and ensure that the measure remains robust to rater and respondent bias.

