### **13.3. Economic analysis**

#### **13.3.1. Short-term cost-effectiveness**

Short-term assessment of cost-effectiveness will take the NHS/Personal Social Services perspective preferred by NICE (23), and will include all hospital and community based health and social services provided for the child over the course of the trial. Data will be recorded in interview with parents at baseline, end of intervention and follow-up assessments using a modified version of the Child and Adolescent Service Use Schedule (CA-SUS), developed and successfully employed in previous evaluations with young people (e.g. 48-49), including pre-school children (50). Data on intervention contacts and other resources will be collected directly from health visitor records and indirect time (time spent on preparation, supervision, administration, travel etc) will be estimated using questionnaires completed by each health visitor delivering the intervention. National unit costs will be applied to all services (54-55), with the exception of the ViPP intervention, which will be costed using a micro-costing approach (56).

Two short-term economic evaluations will be undertaken:

- i) cost-effectiveness analysis using the primary outcome measure of the trial (Pre-PACS)
- ii) cost-consequences analysis, outlining the costs alongside all secondary outcome measures in order to explore potential economic impacts of the intervention more broadly. No method of direct estimation of health-related quality of life, and thus quality adjusted life years (QALYs), currently exists for infants and pre-school children, so it is not possible to undertake a cost-utility analysis at this stage. However, the feasibility of using modelling to explore longer-term cost-utility will be explored, as described below.

For the cost-effectiveness analysis, incremental cost-effectiveness ratios will be reported and uncertainty explored using cost-effectiveness acceptability curves (57-59).

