**Parental/ care-giver Sensitivity\***

Baseline

5 month follow-up

24 month follow-up

Treatment effect is the difference in mean between treatment groups from regression analysis of the outcome measure on the baseline score of that same measurement, on treatment centre, on randomised group, on length of follow-up, on age of child and on number of parents/ care-givers participating (all treated as fixed effects).

Where any child has two male or two female care-givers, their scores will be averaged prior to inclusion in the above analysis, to avoid violating the assumption of independence.

**Changes from official signed draft:** AUDIT assessment of alcohol consumption has been removed from this table.

1941  
1942

8.13 Table: Attendance at Sessions and Satisfaction with Treatment amongst those allocated to the ViPP group

|                                                                                                   | One parent/ care-giver
agreed to participate

n (%) | Two parents/ care-givers agreed to
participate |                     |
|---------------------------------------------------------------------------------------------------|--------------------------------------------------------------|---------------------------------------------------|---------------------|
|                                                                                                   |                                                              | First

n (%)                                | Second

n (%) |
| Attended all sessions                                                                             |                                                              |                                                   |                     |
| Number of session attended                                                                        |                                                              |                                                   |                     |
|                                                                                                   | 5                                                            |                                                   |                     |

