|                                                                                                   | 4                                                            |                                                   |                     |
|                                                                                                   | 3                                                            |                                                   |                     |
|                                                                                                   | 2                                                            |                                                   |                     |
|                                                                                                   | 1                                                            |                                                   |                     |
|                                                                                                   | 0                                                            |                                                   |                     |
| Satisfaction, questionnaire scores, amongst those who attended at least one session: n: mean (SD) |                                                              |                                                   |                     |
| Overall score                                                                                     |                                                              |                                                   |                     |
| Helpfulness                                                                                       |                                                              |                                                   |                     |
| Enjoyableness                                                                                     |                                                              |                                                   |                     |
| Relevance                                                                                         |                                                              |                                                   |                     |

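### A feedback form about the intervention is scheduled at the blinded 5-month visit, and nothing requires the PPACS to be scored first or the form to bypass the assessor

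*Combined protocol and SAP*

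**What the plan says.** **Feedback form.** Protocol 11.8.17: "A brief feedback questionnaire will be given to parents at the 5-month follow-up visit". On content: "Questions explore participant satisfaction and experience of the intervention's helpfulness, enjoyableness, relevance, and format". The schedules in protocol 11.6 and SAP 3.9 both place it at 5 months only. SAP Table 8.13 is titled "Attendance at Sessions and Satisfaction with Treatment amongst those allocated to the ViPP group", and its satisfaction rows are limited to families who attended at least one session.

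**Who runs the visit.** Protocol 11.5: "Follow-up assessments will be undertaken in the family home by research assistants who are blind to treatment" allocation. Under 11.3, parents know their allocation.

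**Primary outcome.** The endpoint is the PPACS (Pre-PACS) at 5 months. Under 11.8.1 the interviewer rates the "severity and frequency of the symptoms on the basis of their professional/clinical judgement and written" definitions and thresholds. The same section says that interviewers are blind, that every interview is recorded, and that recordings are checked periodically for drift and bias. SAP 6.6 adds second ratings of 30 recorded interviews at each time point, for an intraclass correlation.

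**CA-SUS.** Protocol 13.3.1: "Data will be recorded in interview with parents at baseline, end of intervention and follow-up assessments". SAP 7.1 has each follow-up interview cover the time since the previous one. ViPP contacts themselves are taken from health visitor records (protocol 13.3.1, SAP 7.2).

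**The concern.** A control family has had no ViPP sessions to rate. A completed form, or a conversation about it, therefore tells the person in the room which arm the family is in. If that person has yet to score the PPACS, the primary outcome is rated with knowledge of allocation.

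Parents are unblinded, so blinding of the interviewer is the main protection against expectation bias. Protocol 11.8.1 relies on investigator-based scoring when it calls the interview more objective than parent questionnaires. Parental sensitivity, emotion regulation and prosocial behaviour (11.8.10, 11.8.13, 11.8.15) are coded from recordings by blinded raters. The primary outcome is scored by the interviewer and lacks that separation.

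**Working it through.** The main check is a comparison of the text; the arithmetic only shows scale.

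**1. Do the elements meet at one visit?** Yes. The feedback form, the PPACS and CA-SUS are all marked at 5 months in protocol 11.6 and SAP 3.9, and 11.5 names only blinded research assistants for follow-up visits.

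**2. Is anything written that keeps them apart?**
- Order of measures: none stated. The row order of the schedule is not an order of administration.
- Who hands out or collects the form, and in which arm: not stated.
- Sealed, postal or online return: not stated.
- Request to parents not to disclose allocation: none.
- Log of unblinding, or the assessor's guess: none. The only unblinding provision, in 11.3, concerns the Chief Investigator after a severe adverse event.
- Analysis: the sensitivity analyses in SAP 6.2 concern missing data and length of follow-up.

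**3. CA-SUS.** From the ViPP visit schedule, the sixth session falls nominally between day 14 + 3×14 + 2×21 = 98 and day 28 + 3×14 + 2×21 = 112. Five months is about 5 × 30.44 = 152 days, so the 5-month recall period covers the nominal course. ViPP is delivered mainly by health visitors (protocol 7.1), so a parent asked about services could mention it. However, health visitor services are also usual care in both arms (7.2), and CA-SUS is not the source of ViPP contact data. Disclosure by this route would be incidental.

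**4. The plan's power figures.** With 120 per arm and a two-sided 5% test (sidedness assumed), the normal approximation gives 79.6% power at 0.36 SD and 90.2% at 0.42 SD; exact t-test power is 79.3% and 90.0%. The stated 80% and 90% are reproduced.

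**5. Scale, under assumptions that are not in the documents.** Let *u* be the share of ViPP interviews scored after unblinding and *b* the shift in those scores favouring ViPP, in SD. Then bias = *u* × *b*. The standard error of the unadjusted difference is √(2/120) = 0.129 SD. With *k* = bias/0.129, two-sided type I error = 1 − Φ(1.96 − *k*) + Φ(−1.96 − *k*).

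| *u* | *b* (SD) | Bias (SD) | Share of 0.36 | Type I error |
|---|---|---|---|---|
| 0 (PPACS always scored first) | any | 0 | 0% | 5.0% |
| 0.25 | 0.1 | 0.025 | 7% | 5.4% |
| 0.5 | 0.1 | 0.05 | 14% | 6.7% |
| 0.5 | 0.2 | 0.10 | 28% | 12.1% |
| 1 | 0.2 | 0.20 | 56% | 34.1% |
| 1 | 0.3 | 0.30 | 83% | 64.2% |

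Covariate adjustment shrinks the standard error, so a given bias would weigh somewhat more. Nothing in the documents says which row applies.

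**6. Timing.** Recruitment ended in July 2017 (SAP 3.7). Adding 5 months and the 3-week window, 5-month visits were due to end around December 2017 to January 2018. SAP 2.0 is dated 7 May 2019. The last 24-month visits fall due about July 2019, or October 2019 with the protocol's 3-month window.

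**The case against.** The strongest reply is that the documents are silent on handling, and silence is not a procedure that unblinds. Section 11.8.17 is in the passive: it does not say that the assessor hands over the form, or when. It says parents, without naming an arm; Table 8.13 shows whose answers are analysed, not who receives a form. If both arms receive one, handing it out reveals nothing, and only a completed form would. All of this stands. A reader might infer that the blinded assessor distributes the form and that unblinding is built in. The text supports neither.

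A reader might also take blinding to be the only protection of the primary outcome. It is not: there are written definitions and thresholds, recordings checked for rater and respondent bias, and second ratings. These are partial. The checkers and second raters are not said to be blind, and no re-rating replaces a score.

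Nor do the documents support treating CA-SUS as a route equal to the form, or quoting a figure such as 14–28% of the design effect as the expected bias. That figure comes from assumed inputs, and zero is also possible.

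Finally, changing the visit procedure now comes too late for the 5-month data. That also stands, and it shapes the fix.

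The reply does not remove the gap. An intervention-specific form is assigned to the visit where a supposedly blind rater scores the primary outcome, and no rule separates the two.

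**Conclusion.** The point holds as a risk that the plan creates and does not mitigate. It is more than a missing detail, because the scheduled procedure brings material that reveals allocation into the blinded visit, and a nearly costless alternative exists. The conclusion rests on the content of the form, its timing, and the absence of any rule on order or return.

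The size of any bias cannot be estimated from the documents. It is zero at 5 months by this route if the PPACS was always scored first, and the table shows only what various assumed degrees of unblinding would do. An assessor who learned the allocation after scoring at 5 months could still carry that knowledge to the 24-month interview if the same person returned; the documents do not say. No figure in the sample size section is wrong, and the sample size does not change.

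**What to change.** **Protocol 11.6 and 11.8.17.**
- Require the PPACS to be completed and scored before any other measure that involves contact with the parent, with CA-SUS last.
- Send the feedback form by post or online once the PPACS score is entered, for return to trial office staff who take no part in outcome assessment.
- Ask parents not to disclose allocation.
- Have the assessor record whether and when allocation became known.

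**Visits already done.** Document the order actually used and report known unblinding by arm. Apply the ordering, non-disclosure and recording rules to any 24-month visits still to come.

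**Analysis.** Do not add a sensitivity analysis that excludes unblinded interviews. Unblinding through the form would fall mainly on ViPP families who attended sessions, so this would be a post-randomisation exclusion, largely from one arm, and would break the intention-to-treat comparison. Where blind second ratings of recordings already exist under SAP 6.6, compare them with the interviewers' scores by arm. With 30 recordings per time point, or about 30/2 = 15 per arm if sampled evenly, this is a coarse check.

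**Cost.** A minor amendment, postage or an online form, and a likely lower return rate for the satisfaction questionnaire. The retrospective steps need only existing records and ratings.

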## **12. Safety Reporting**

### **12.1. Adverse Event (AE)**

An AE is any untoward medical occurrence which does not necessarily have a causal relationship with the trial treatment. An AE can therefore be any unfavourable and unintended sign (including an abnormal laboratory finding), symptom, or disease temporally associated with the trial treatment, whether or not considered related to the treatment.

### **12.2. Severity of Adverse Events**

Severity of AEs will be assessed according to the following definitions:

Mild: Awareness of event but easily tolerated  
 Moderate: Discomfort enough to cause some interference with usual activity  
 Severe: Inability to carry out usual activity, including play for infants and children

